### **7.3.3 QuantiFERON Conversion Rate**

QuantiFERON®-TB Gold In-Tube test results through the end of the study will be summarized by number (percentage) of positive responses by ART status at baseline and treatment group. Descriptive statistics will also be used to summarize quantitative QuantiFERON data (IU/mL interferon results) by ART status at baseline, treatment group, and study visit. Cross-tabulation of the number of subjects with a negative baseline QuantiFERON with subsequent conversion to a positive result post-vaccination through the end of study will be summarized by ART status and treatment group, based on the PP population. The exact binomial (Clopper-Pearson) method will be used to estimate VE and its corresponding two-sided 95% confidence interval conditional on the total number of events, and corresponding p-value.

## **7.4 Safety Analyses**

Safety analyses will be performed using the safety population as defined in Section 7.1. Count (percentage) summaries will be presented by treatment group for all subjects in the safety population.

### **7.4.1 Adverse Events**

The safety profile of MVA85A/AERAS-485 will be evaluated based on the number and percentage of solicited and unsolicited adverse events (including serious adverse events [SAEs]) recorded over the post-vaccination follow-up period for all subjects in the safety population. The number (percentage) of subjects with adverse events will be summarized by MedDRA system organ class (SOC) and preferred term (PT). The proportion of subjects in the control and MVA85A/AERAS-485 treatment groups with at least one adverse event will be compared using Fisher's Exact test; two-sided exact 95% confidence intervals will also be presented for proportions of individual adverse event preferred terms, within treatment group. Supportive summaries by ART status will also be presented. Additional summaries will present the number (percentage) of subjects with adverse events by severity and by relationship to study vaccine; each subject will be counted once per preferred term at the greatest severity or most related state recorded for that term. Separate summaries of the number (percentage) of subjects with solicited adverse events will also be presented. Solicited adverse events will also be summarized by severity and relationship to study vaccine; each subject will be counted once per preferred term at the greatest severity or most related state recorded for that term.

Separate summaries for the number (percentage) of deaths, subjects with serious adverse events, and subjects with HIV-related opportunistic infections or other adverse events will also be presented by ART status at baseline, study site, and treatment group. Listings of subjects who discontinued prematurely due to an adverse event will also be provided.

The number (percentage) of subjects with post-vaccination clinical laboratory values or vital sign values recorded as newly abnormal following study vaccination and meeting toxicity mild criteria (Grade 1) or above as specified in the Toxicity Table (Appendix C) will be tabulated at each post-vaccination time point and overall. Clinical laboratory and vital sign abnormalities will also be reported as adverse events and will be included in the summary of adverse events.

#### **7.4.2 Clinical Laboratory and Vital Sign Parameters**

For each clinical laboratory parameter and vital sign parameter pre-specified in the protocol, summary statistics for continuous parameters will be presented by treatment for all pre- and post-vaccination assessments and for change from pre-vaccination to post-vaccination assessments.

#### **7.4.3 CD4+ Lymphocyte Count**

Median or geometric mean CD4+ lymphocyte counts and associated two-sided 95% confidence interval will be summarized by ART status at baseline, study site, treatment group, and time point, for subjects in the safety population. Summaries will include change in CD4+ lymphocyte count from pre-vaccination to each post-vaccination time point. Area under the curve will also be used to summarize CD4+ lymphocyte count by treatment group across pre- and post-vaccination time points based on the trapezoidal rule, within strata. Any impact of MVA85A/AERAS-485 vaccination on CD4+ lymphocyte count compared with placebo will be explored using the AUC in a mixed effects model including treatment group, Study Day 0 CD4+ count, age, baseline ART status, and study site. Data for CD4+ lymphocyte count will be log-transformed prior to analysis as appropriate.

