### **CD4+ Lymphocyte Count**

Median or geometric mean CD4+ lymphocyte counts and associated two-sided 95% confidence interval will be summarized by ART status at baseline, study site, treatment group, and time point. Summaries will include change in CD4+ lymphocyte count from pre-vaccination to each post-vaccination time point. Difference in CD4+ count between treatment groups over the course of the study will be evaluated using an area under the curve (AUC) and associated two-sided 95% CIs.

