#### **3.6.2 Clinical Assessments and Laboratory Tests**

An examination of the injection site will be performed 60 minutes after each study vaccine/placebo administration and at 7 and 28 days after each vaccination. Subjects will have CD4+ lymphocyte counts done prior to each vaccination, at 7, 28, and 84 days after each vaccination and then at 6 months post-boost. Vital signs will be recorded prior to each vaccination, at 7, 28, 84 days after each vaccination, and at all subsequent study visits. Subjects will also have tests done for HIV-1 viral load results done prior to each vaccination, at 7 and 28 days after each vaccination, and then at 6 months post-boost.

Blood for hematology and serum chemistry will be collected at screening and prior to booster vaccination and 7 and 28 days after each vaccination. All laboratory samples will be processed according to SOPs provided by the local clinical laboratory.

All subjects randomized to the study will have a Tuberculin PPD skin test and blood for QFT-G collected during screening, and then again at the End of Study visit. Subjects will also be observed for signs and symptoms of TB at every study visit.

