#### **Post-vaccination:**

- Monitor subject for solicited, unsolicited, and serious adverse events for at least 60 minutes after vaccination (including concomitant medications)
- Obtain 60-minute post-immunization vital signs
- Complete site of injection examination
- Distribute diary cards and review diary card instructions

**Study Visit 1 -** *Allowable window for clinic visit is 7 ±2 days from Study Day 0 (Randomization/initial vaccination).*

- Obtain vital signs
- Review and record any solicited, unsolicited, and serious adverse events (including concomitant medications)
- Monitor subject for clinical observations for signs and symptoms of TB
- Review and record diary card entries for completeness and accuracy
- Complete site of injection examination
- Blood collection for
  - Serum chemistry (GGT, ALT, AST, total bilirubin, ALP, creatinine)
  - Hematology (CBC, differential, platelets)
  - CD4+ lymphocyte count
  - HIV-1 viral load
  - Immunology samples

**Study Visit 2 -** *Allowable window for clinic visit is 28 ±3 days from Study Day 0 (Randomization/initial vaccination).*

- Obtain vital signs
- Review and record any solicited, unsolicited, and serious adverse events (including concomitant medications)
- Monitor subject for clinical observations for signs and symptoms of TB
- Complete site of injection examination
- Blood collection for
  - Serum chemistry (GGT, ALT, AST, total bilirubin, ALP, creatinine)
  - Hematology (CBC, differential, platelets)
  - CD4+ lymphocyte count
  - HIV-1 viral load
  - Immunology samples

**Study Visit 3 -** *Allowable window for clinic visit is 84±7 days from Study Day 0 (Randomization/initial vaccination).*

- Obtain vital signs
- Monitor subject for clinical observations for signs and symptoms of TB
- Review and record any serious adverse events (including concomitant medications)
- Blood collection for
  - CD4+ lymphocyte count

**Study Visit 4 – Booster Vaccination-** *Allowable window for visit is 168 to 252 days from Study Day 0 (Randomization/initial vaccination).*

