**Study Visit 7 - Allowable window for clinic visit is  $84 \pm 7$  days from SV4 (booster vaccination visit).**

- Obtain vital signs
- Monitor subject for clinical observations for signs and symptoms of TB
- Review and record any serious adverse events (including concomitant medications)
- Blood collection for
  - CD4+ lymphocyte count

**Study Visit 8 until End of Study Visit** – *Allowable window for clinic visit is every 3 months  $\pm$  7 days from SV4 (booster vaccination visit)*

- Obtain vital signs
- Monitor subject for clinical observations for signs and symptoms of TB
- Review and record any serious adverse events (including concomitant medications)
- Blood collection for
  - CD4+ lymphocyte count (at 6 months post-boost)
  - HIV-1 viral load (at 6 months post-boost)

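### The one modelled CD4 comparison with placebo is a whole-study AUC that is insensitive to a short-lived fall after vaccination; visit-specific treatment differences should be added beside it

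*Protocol*

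**What the plan says.** Secondary objective 2 (section 2.1) is to evaluate CD4 counts and viral load before and after vaccination, compared with placebo.

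For CD4, section 7.4.3 names one method for the comparison between arms. The effect of vaccination "will be explored using the AUC in a mixed effects model including treatment group, Study Day 0 CD4+ count"; the other covariates are age, ART status at baseline and site. The AUC is taken "across pre- and post-vaccination time points based on the trapezoidal rule". The Study Abstract, under CD4+ Lymphocyte Count, also evaluates the treatment difference by an AUC across the whole study, with two-sided 95% CIs.

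The same section requires descriptive output: median or geometric mean CD4 with a 95% CI by ART status, site, treatment group and time point. It adds: "Summaries will include change in CD4+ lymphocyte count from pre-vaccination to each post-vaccination time point".

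On sampling, section 3.6.2 has "CD4+ lymphocyte counts done prior to each vaccination, at 7, 28, and 84 days after each vaccination and then at 6 months post-boost". For the booster, Appendix A (Study Visit 4) states: "Allowable window for visit is 168 to 252 days from Study Day 0".

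Sections 5.1.5 and 7.8 have the DMC review safety data unblinded by group, CD4 counts included. The two scheduled reviews follow one month of follow-up after the primary vaccination for the 200th and the 600th subject.

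**The concern.** A trapezoidal AUC weights each sample by the time gap around it. CD4 is sampled closely just after each injection and sparsely later, so the earliest post-dose samples get little weight and the late ones get most of it. A fall that appears at Day 7 and has recovered by Day 28 barely moves the result.

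The participants are HIV-infected, safety is the primary objective, and the rationale (section 1.5) cites the absence of a clinically significant CD4 effect in earlier trials. A null AUC could be taken as confirming that for the period just after each dose, although the analysis has little ability to detect a brief change there.

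**Working it through.** **The protocol's own figures.** No CD4 power and no AUC weights are stated. The only safety sample-size figure (section 7.6) is a 90% probability of seeing at least one event of rate 0.71% in 325 vaccinees. It reproduces, 1 − (1 − 0.0071)^325 = 0.901, but says nothing about CD4.

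**Inputs from the protocol.** With booster day B = 168 to 252, the sampling days are 0, 7, 28, 84, B, B+7, B+28, B+84 and B+6 months. Six months is taken as 182 days, with 168 days tried as a variant. Arm size is 325.

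**Assumptions.** The SD is 205 cells/mm³ (the overall baseline SDs in Table S1 run from 169.8 to 220.7). Within-subject correlation ρ is 0.6-0.8 with compound symmetry. Analysis is on the raw scale with a two-sided 5% test. The AUC is divided by its length and is the same length for all subjects. The fall occurs after both doses.

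**Step 1, weights.** The weight of a sample is half the distance between its neighbours, divided by the total length.

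- Each Day 7 sample: (28 − 0)/2 = 14 days, so 28 days for both.
- Each Day 28 sample: (84 − 7)/2 = 38.5 days, so 77 days for both.

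| | B = 168 | B = 252 |
|---|---|---|
| Length | 168 + 182 = 350 days (11.5 months) | 252 + 182 = 434 days (14.3 months) |
| Day 7, both | 28/350 = 8.0% | 28/434 = 6.5% |
| Day 28, both | 77/350 = 22.0% | 77/434 = 17.7% |
| Days 7 and 28 | 30.0% | 24.2% |

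With a last sample at B + 168 and B = 168, the length is 336 days (11.0 months) and the shares are 8.3% and 31.3%. Visit windows move the Day 7 share to about 5.7-9.4%. If both pre-dose samples are 14 days early, as the protocol allows, it is about 12%.

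**Step 2, standard errors.** For the time-averaged AUC adjusted for Day 0, with weights w:

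residual variance = σ²{[ρ + (1−ρ)Σw²] − [ρ + (1−ρ)w₀]²}.

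With B = 168 and ρ = 0.6, Σw² = 0.1524 and w₀ = 0.010. This gives 0.661 − 0.604² = 0.296, a residual SD of 205 × √0.296 = 111.6, and an SE of 111.6 × √(2/325) = 8.75. Over B = 168-252 and ρ = 0.6-0.8, the SE is 7.0-8.9.

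For a single Day 7 visit adjusted for Day 0, the residual SD is 205√(1−ρ²). That is 164 at ρ = 0.6 and 123 at ρ = 0.8, with SEs of 12.9 and 9.6.

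**Step 3, power** (normal approximation).

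| Fall | Shift in AUC mean (cells) | AUC power | Day 7 contrast power |
|---|---|---|---|
| 50 cells, Day 7 only | 3.2-4.0 | about 7-9% | 97% or more |
| 100 cells, Day 7 only | 6.5-8.0 | 11-21% | over 99% |
| 50 cells, through Day 28 | 12.1-15.0 | 28-58% | 97% or more |
| 100 cells, through Day 28 | 24.2-30.0 | 78-99% | over 99% |

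The Day 7 contrast uses one dose only. The AUC figures already count the fall after both.

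**The case against.** The strongest reply is that the AUC is one output among several, and four parts of it stand.

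- **The arms are also compared descriptively.** A reader might infer that an acute fall would vanish from the report. It would not, because section 7.4.3 tabulates levels with CIs, and changes, by arm at every visit. With SD 205, the 95% half-width of a mean is 1.96 × 205/√325 = 22 cells for a whole arm, so a 100-cell fall would be plain. What is missing is an estimated, baseline-adjusted treatment difference with its CI. If the tables cross ART status with site, some cells are small: Table S1 implies 146 − 109 = 37 ART-negative placebo subjects in Cape Town.
- **The DMC sees CD4 by group.** This covers the weeks after the first dose. Neither scheduled review is triggered by the booster, and neither supplies the final estimate for objective 2.
- **A whole-study average is a legitimate target, and efficient for a lasting effect.** For a sustained fall the AUC is the more powerful analysis (SE 7.0-8.9 against 9.6-12.9). A reader might infer that the schedule was designed to catch an acute fall, so that the AUC defeats its purpose. No section states such a purpose, and CD4 is also drawn at 84 days after each dose, before the boost and at 6 months post-boost.
- **The SAP may add more.** Sections 7 and 7.9 allow this, and the SAP is not at hand. The point is therefore limited to what the protocol fixes: it names the AUC for this comparison in two places.

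**Conclusion.** The point holds in a limited form. The only inferential between-arm CD4 comparison the protocol specifies is diluted roughly 12- to 16-fold (1/0.080 to 1/0.065) for a fall confined to Day 7, and roughly 3- to 4-fold for one lasting through Day 28. A 50-cell fall at Day 7 alone would very probably leave the AUC result null. A 100-cell fall lasting through Day 28 would probably be detected.

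The weights follow from the visit schedule. The power figures rest on the assumed SD, correlation, compound symmetry and raw scale; section 7.4.3 allows a log transformation, which would change them. At ρ = 0.9 and SD 200, AUC power for 50 cells at Day 7 only is still 9-13%.

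The documents do not support saying that a fall would go unseen, or that the AUC is the wrong analysis and should be demoted. They support adding an estimate of the acute difference.

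**What to change.** Keep the AUC model in section 7.4.3 for the overall effect. Add MVA85A-placebo differences with 95% CIs at Days 7 and 28 after each vaccination, ideally at every CD4 visit. Take them from a treatment-by-visit repeated-measures model, or from ANCOVA, on log CD4, adjusted for the pre-dose CD4 of that vaccination (Day 0 or SV4), ART status and site. State beside the AUC result that it describes the average over the whole period.

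The cost is a few lines in section 7.4.3 and the SAP, with no new samples or visits. It yields several time-point estimates without multiplicity control, so they should be reported as estimates with CIs and not as a set of tests. The SV4 value is measured after randomization, so the post-boost contrasts describe the difference beyond the pre-boost level among boosted subjects, and should be labelled so.

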#### **7.4.4 HIV-1 Viral Load**

HIV-1 viral load (copies/mL) will be summarized using the median and associated 95% confidence interval by ART status at baseline, study site, and treatment group, at each available time point, for subjects in the safety population. Summaries will include change from pre-vaccination to post-vaccination time points. Additional summaries and comparisons of the mean AUC of MVA85A/AERAS-485 and placebo, as described for CD4+ lymphocytes, will also be performed.

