|                                          | Missing | 6 (1.8)         | 10 (3.1)         | 6 (4.1)         | 10 (6.8)         | 0 (0.0)          |
| Latently infected*; n (%)                |         | 178 (54.8)      | 164 (50.6)       | 87 (59.6)       | 89 (61.0)        | 91 (50.8)        |
| 5-6 months IPT prior to enrolment; n (%) |         | 144 (44.3)      | 133 (41.0)       | 68 (46.6)       | 69 (47.3)        | 76 (42.5)        |
| Receiving ART; n (%)                     |         | 256 (78.8)      | 257 (79.3)       | 109 (74.7)      | 110 (75.3)       | 147 (82.1)       |
| CD4 (cells/mm  ); mean (SD)  | ART-    | 564 (169.8)     | 571 (187.5)      | 572 (176.5)     | 578 (202.7)      | 554 (164.0)      |
|                                          | ART+    | 599 (199.6)     | 598 (220.7)      | 637 (192.3)     | 632 (251.2)      | 571 (200.8)      |
| HIV viral load (copies/ml); mean (SD)    | ART-    | 41371 (92456.9) | 62168 (166912.1) | 20944 (40176.7) | 77807 (215689.5) | 65753 (126590.7) |
|                                          | ART+    |                 |                  |                 |                  |                  |

|      |           |           |          |          |           |           |
|------|-----------|-----------|----------|----------|-----------|-----------|
| ART+ | 29 (27.1) | 34 (63.7) | 25 (0.0) | 25 (3.3) | 32 (35.9) | 40 (84.2) |
|------|-----------|-----------|----------|----------|-----------|-----------|

QFT: QuantiFERON® Gold In-Tube; IPT: isoniazid preventive therapy; ART: antiretroviral therapy

\* TST (PPD skin test) >5mm or QFT positive

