**Subjects must meet all of the following criteria at the time of randomization:**

1. Has completed the written informed consent process prior to undergoing any screening evaluations.
2. Either males or females aged  $\geq 18$  and  $\leq 50$  years on Study Day 0
3. In general good health, confirmed by medical history and physical examination
4. Has ability to complete follow-up period as required by the protocol
5. Has laboratory evidence of human immunodeficiency virus (HIV) infection, defined as a positive HIV-1 ELISA test plus a positive confirmatory test (e.g., a second HIV-1 ELISA, PCR, or rapid ELISA) diagnosed prior to randomization
6. Is willing to allow the investigators to discuss the subject's medical history with the subject's HIV physician
7. If not receiving ART at the time of randomization, must have 2 CD4+ lymphocyte count test results  $>350$  cells/mm^3, performed at least 4 weeks apart, one performed within 6 months prior to randomization and one within 45 days prior to randomization
8. If receiving antiretroviral therapies (ART) at the time of randomization, must have 2 CD4+ lymphocyte count test results  $>300$  cells/mm^3, performed at least 4 weeks apart, one performed within 6 months prior to randomization and one within 45 days prior to randomization
  - a. Subjects on ART must have been receiving ART for at least 6 months prior to randomization and must have an undetectable HIV viral load within 45 days prior to randomization
  - b. Women who received ART as part of the PMTCT program must have completed therapy at least 2 months prior to randomization
9. Has either
  - a. a negative QuantiFERON-TB Gold In-Tube test result and tuberculin PPD skin test  $\leq 5$  mm induration within 45 days prior to randomization or

- b. a positive QuantiFERON-TB Gold In-Tube test result and/or tuberculin PPD skin test >5 mm and has completed at least 5 months of isoniazid preventive therapy within 3 years prior to randomization or
  - c. a positive QuantiFERON-TB Gold In-Tube test result and/or tuberculin PPD skin test >5 mm and has completed treatment for TB disease within 3 years prior to randomization

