#### **5.15 Follow-up of Subjects Who Become Pregnant**

If a subject becomes pregnant during the study, she should be encouraged to continue in the study for safety follow-up and for TB disease according to the protocol. Follow-up should continue for pregnancy outcome including premature terminations, and data are to be included in the safety reports.

The investigator must notify the local medical monitor, World Wide Safety Center and CRO, Triclinium, of the pregnancy immediately (even if already known to have resulted in

spontaneous or elective abortion) by emailing/faxing the Pregnancy Form to the medical monitor. At a minimum, the estimated date of conception, the estimated due date, and the date the subject received the study vaccine should be provided.

If a subject becomes pregnant, she will not have blood drawn as normally mandated by the protocol. The subject will undergo all other evaluations according to the Summary Schedule(s) of Evaluations.

The health status of the mother and child, the date of delivery, and the child's sex, birth weight and multiparity should be reported to the safety monitor after delivery. If delivery occurs before the final study visit, the subject should continue to be followed for SAEs through the final study visit unless withdrawal of consent has occurred. If delivery occurs after the final study visit, the investigator should attempt to maintain contact with the subject to obtain information after delivery.

Pregnancy will not be recorded as an adverse event. However, pregnancies will be recorded in the World Wide Safety Database. If the pregnancy results in a miscarriage, the event (spontaneous abortion) will be reported as an adverse event or a serious adverse event per the investigator's judgment (e.g., if it was a medically important or life-threatening event that meets the definition of a serious adverse event).

A congenital anomaly or birth defect (i.e., an adverse finding in a child or fetus of a subject exposed to the study vaccine before conception or during pregnancy) must be reported as a serious adverse event.

If it is determined after completion of the study that a subject became pregnant during the study, the subject should notify the investigator. The pregnancy must be reported to the local medical monitor and the status of the mother and child after delivery will be obtained and reported, when possible.

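### In the ART+ stratum the planned viral-load medians cannot show loss of suppression in a minority; add the proportion detectable by arm and put the viral-load AUC on the log10 scale

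*Protocol*

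**What the plan says.** Secondary objective 2 (Protocol 2.1) is to evaluate CD4+ count and HIV-1 viral load before and after vaccination, against placebo.

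- **Summary statistic (7.4.4).** "HIV-1 viral load (copies/mL) will be summarized using the median and associated 95% confidence interval by ART status at baseline", and also by site, arm and visit. It adds: "Summaries will include change from pre-vaccination to post-vaccination time points". The Study Abstract repeats the median summary.
- **Comparison between arms (7.4.4).** "Additional summaries and comparisons of the mean AUC of MVA85A/AERAS-485 and placebo, as described for CD4+ lymphocytes, will also be performed". Section 7.4.3 defines that AUC "by treatment group across pre- and post-vaccination time points based on the trapezoidal rule, within strata". It is modelled with treatment, Study Day 0 count, age, ART status and site. Section 7.4.3 allows a log transform of CD4+ data where appropriate; 7.4.4 names no transform for viral load.
- **Entry condition (3.2.3, criterion 8a).** Each ART+ subject "must have an undetectable HIV viral load within 45 days prior to randomization".
- **Size of the stratum.** Section 2.2 caps randomization so that at least half the subjects are on ART. Table S1 shows 256 placebo and 257 MVA85A subjects on ART.
- **Baseline values.** Mean (SD) viral load in ART+ subjects, placebo then MVA85A, first overall and then in Cape Town, reads "29 (27.1) | 34 (63.7) | 25 (0.0) | 25 (3.3"). An SD of zero or near zero at a mean of 25 is what a reporting floor looks like.

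**The concern.** The median is a good summary of a skewed distribution, but a poor one when nearly every value in the stratum sits at the floor by eligibility. Only a subject who loses suppression carries information there, and the median ignores those subjects until they are about half the group. Median change fails in the same way, because a subject who stays at the floor has a change of zero.

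Section 1.5 relies on there having been no clinically significant effect of the vaccine on viral load. In the ART+ stratum, which is most of the trial, the planned table could repeat that reassurance while a sizeable minority of vaccinees had become viraemic. The newly abnormal laboratory tabulation in 7.4.1 does not fill the gap, because it uses Appendix C, which has no viral-load row.

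**Working it through.** Section 7.4.4 states no figure to reproduce. The protocol's one safety precision figure (7.6) does reproduce and is not in question: 1 − (1 − 0.0071)^325 = 0.901, against 90% stated.

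**1. When does the median move?** Let n subjects start at the floor and k rebound. The sample median leaves the floor at k = n/2 (n even) or (n+1)/2 (n odd). The exact 95% CI for a median runs from rank l to rank n+1−l, where l is the largest integer with P(Bin(n, 0.5) ≤ l−1) ≤ 0.025. The upper limit leaves the floor at k = l.

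| ART+ group | n | Median moves at | CI ranks | Upper limit moves at |
|---|---|---|---|---|
| Placebo, observed | 256 | 128 (50.0%) | 112, 145 | 112 (43.8%) |
| MVA85A, observed | 257 | 129 (50.2%) | 113, 145 | 113 (44.0%) |
| Planned minimum, half of 325 | 163 | 82 (50.3%) | 69, 95 | 69 (42.3%) |
| Cape Town placebo | 109 | 55 (50.5%) | 44, 66 | 44 (40.4%) |
| Cape Town MVA85A | 110 | 55 (50.0%) | 45, 66 | 45 (40.9%) |
| Dakar placebo | 147 | 74 (50.3%) | 62, 86 | 62 (42.2%) |

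Rebound in 20%, 30% or 40% of ART+ vaccinees therefore leaves the median and its CI at the floor in every row.

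**2. What would the proportion detectable show?** With 256 against 257 subjects, Fisher's exact test at two-sided 5% has 96.5% power for 5% versus 15% detectable, and 79% for 5% versus 12%. The rates are assumptions. In both cases the medians and their CIs stay at the floor in both arms.

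**3. Does the AUC fill the gap?** It depends on the scale. In simulations with assumed rebound levels, a log10 AUC pooled over ART strata had 88% power for 5% versus 15% rebound and about 100% for 5% versus 25%. A raw copies/mL AUC had only 2–13%. The exact figures move with the assumed level and timing of rebound.

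A rough calculation shows why. Take 10 percentage points more rebound in ART+ vaccinees, to 1,000 copies/mL from a floor of 25. The arm mean rises by 0.10 × 975 × 257/324 ≈ 77 copies/mL; at 10,000 copies/mL it rises by about 791. Using the Table S1 baseline SDs, ART- subjects alone contribute these standard errors to the arm means:

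- Placebo: (69/325) × 92,456.9/√69 ≈ 2,363.
- MVA85A: (67/324) × 166,912.1/√67 ≈ 4,217.
- Difference: √(2,363² + 4,217²) ≈ 4,834 copies/mL.

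Baseline adjustment reduces this. But 80% power for a shift of 791 needs a standard error near 791/2.8 ≈ 283, some 17 times smaller. Baseline would have to explain over 99% of the ART- variance.

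**4. AUC span.** The booster may fall on day 168 to 252 (Appendix A) and the last sample is 6 months later, taken here as 168 to 182 days. Complete series run from 168 + 168 = 336 to 252 + 182 = 434 days. At one constant value, booster timing alone changes a raw AUC by 420/336 = 1.25 or 434/350 = 1.24. In a simulation of CD4+ AUC under assumed variance components, this added about 15% to the variance compared with a time-averaged AUC.

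**The case against.** The strongest reply is that the medians are only descriptive. The planned comparison between arms is of mean AUC, which responds to rebound in a minority. In an ART+ only simulation (floor 25, persistent rebound at a median of 1,000 or 10,000 copies/mL, complete data), an unstandardised log10 AUC had 90–94% power for 5% versus 15% and about 100% for 5% versus 25%. This stands. A reader might infer that the plan would miss large-scale rebound altogether, and the protocol does not support that. What the reply needs, and 7.4.4 does not fix, is the log scale.

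A reader might also take 44% as the point at which the median moves. It is the point for the upper confidence limit, and it depends on n; the median itself moves at about 50%.

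On the AUC, a reader might infer that the CD4+ comparison would mainly measure length of follow-up. It would not. The booster window is balanced by randomization and adds noise; bias arises only if timing or dropout differs by arm. Severe losses of power appear only if truncated series are assumed to be kept as partial AUCs, a rule the protocol does not state. Pregnancy ("If a subject becomes pregnant, she will not have blood drawn as normally mandated by the protocol") is a limited source of truncation, because criterion 10 requires avoiding pregnancy through 6 months after the last dose, which is when the last sample falls.

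Finally, the statistical analysis plan is not shown and may add a proportion-detectable table or a time-averaged AUC. That limits the AUC-span point in particular. It does not remove the main one, because the median is what the protocol itself specifies, in both 7.4.4 and the Abstract.

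**Conclusion.** The point holds for ART+ subjects. The planned median, its CI and the median change cannot show loss of suppression in a minority: about 50% must rebound before the median moves, and about 44% before its upper limit does (42% at the planned minimum ART+ share, 40–42% in the by-site tables). The planned AUC comparison can detect such rebound if it is done on log10 values, and would have little chance if done on raw copies/mL pooled over strata. Time-averaging the AUC is a secondary gain in precision.

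Assumptions: all ART+ subjects start at the floor, which criterion 8a implies and Table S1 broadly supports (the Dakar SDs of 35.9 and 84.2 show a few above it). The floor of 25 is read from Table S1, since the protocol does not state it. The counts 256 and 257 are observed; at planning only the 50% minimum was known. The power figures rest on assumed rebound rates and levels. In ART- subjects, with mean baseline viral loads of 41,371 and 62,168 copies/mL, the median remains suitable.

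**What to change.** In 7.4.4 and the Abstract:

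1. For ART+ subjects, report at each post-vaccination visit the number and percentage above the detection limit used for entry, by arm, with the MVA85A minus placebo risk difference and 95% CI stratified by site. State that limit.
2. Keep medians for ART- subjects.
3. State that the viral-load AUC is computed and compared on log10 values.

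Secondary, in 7.4.3 and 7.4.4: divide each AUC by the subject's observed time before modelling.

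The cost is one added table and two lines of definition. No visit, sample or assay changes, since viral load is already measured at every time point needed.
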